### Safety assessments

2.7

During the study period, participants will be continuously monitored for adverse reactions. In addition, symptoms and vital signs will be recorded, routine physical examinations will be given, and complete blood tests will be done according to the National Cancer Institute Common Terminology Criteria for Adverse Events, version 4.03 (NCI CTCAE v4.03).^[12]^ These will be done before, during, and after the 12-week trial. If no adverse reactions occur, all assessments will be completed during the last visit. At each visit, participants will be questioned, and all adverse events will be recorded; all reported adverse events will be analyzed. Safety and tolerability will be assessed according to the NCI CTCAE v4.03.

### Randomization and blinding

2.8

After informed consent has been obtained, random assignment will be performed by using a computer-generated, blocked, random-allocation sequence with a 1:1:1 ratio. Each participant will be assigned to a group according to a pre-generated randomization table and an assigned randomized number. Each participant will be assigned to treatment group 1, treatment group 2, or the control according to the allocation codes of the randomized assignment method, which will be prepared in advance. In order to maintain a double-blind trial, we will use the same formulations and properties for the placebo so that it is indistinguishable from the test drug. The allocation of unique codes for each group will be managed by the managing pharmacist, will be kept in a sealed envelope, and will not be disclosed until the end of the clinical trial.

### Sample size calculation

2.9

The sample size was determined by considering the number of participants available, the minimum range of the efficacy assessment, and the expected dropout rate during the study period. When the first two factors were considered, the total number of participants required for each group was calculated as 15, for a total of 45. When a dropout rate of 30% was used for each group, the required number of participants was calculated as 22 (15/(1 – 0.3) = 21.43 ≒ 22). Thus, when all factors are considered, the number of participants to be registered for each group is 22, so a total of 66 patients will be recruited.

### Statistical analysis

2.10

#### Analysis group

2.10.1

The data obtained from the subjects of this clinical trial will mostly be divided into a safety group, a FAS (full analysis) group and a PP (per protocol) group. The safety group will include participants who took the HAD-B1 or the placebo at least once. The FAS group will include participants who received the clinical trial medication, followed by one or more measurements of the primary outcome. Participants in FAS group who violate major inclusion, exclusion criteria or have never taken drug for clinical trial can be excluded. The PP group will include participants from among the FAS group who successfully completed this clinical trial according to the trial plan. Participants in PP group who violate test plan or take forbidden drug or do not obey a schedule can be excluded.

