### Interventions

2.5

Patients in the treatment group 1 will receive afatinib (40 mg/day orally) plus HAD-B1 2 tablets (972 mg/day, bid orally) and placebo 2 tablets, those in the treatment group 2 will receive afatinib (40 mg/day orally) plus HAD-B1 4 tablets (1944 mg/day, bid orally), while those in the control group will receive afatinib (40 mg/day orally) plus placebo 4 tablets (bid orally). Afatinib, HAD-B1 and/or placebo will be administered consistently for 12 weeks; the trial may be terminated before the end of 12 weeks due to the development of unacceptable toxicities or withdrawal of the participant from the treatment.

The HAD-B1 tablets used in clinical trial will purchased from the Gyeongbang Pharmaceutical Co., Ltd. (In-cheon, Korean) and will meet the requirements of Good Manufacturing Practice (GMP). HAD-B1 is a medical substance that contains *Panax ginseng C.A.* (640 mg), *Panax notoginseng Radix* (839 mg), *Cordyceps militaris* (640 mg), and *Boswellia carterii BIRDWOOD* (480 mg) as raw material medicines is extracted for 16 hin purified water at 60°C. Then, the filtrate is concentrated under reduced pressure to obtain a dry extract of 486 mg. From this, 650 mg of one brown film-coated tablet is produced by adding excipients.^[10]^ The matching placebo will be purchased from the same manufacturer and consist of starch with no active ingredients.

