### Outcome measures

2.6

The primary outcome is a comparison of the disease control rates (DCR) among treatment groups 1 and 2 and the control group after 12 weeks compared to baseline, which will be assessed from the date of randomization to 12 weeks, as determined by chest X-ray, CT or MRI according to the RECIST criteria.^[11]^

The secondary outcomes are comparisons of the complete response (CR) and the partial response (PR) to the treatment, the stability of the disease (SD), progression free survival (PFS), time to progression (TTP), and tumor marker (CEA, NSE) and WBC differential count (LMR, NLR) and natural killer cell activity and QOL (EORTC QLQ-C30) among treatment groups 1 and 2 and the control group after 6 weeks and 12 weeks compared to baseline.

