### Principles of interpretation of results

2.11

The main analysis will be the FAS group analysis for the validity evaluation. The PP group analysis will be carried out separately to evaluate whether or not any differences from the FAS analysis results exist. For the FAS group, if a defect value happens at any point or a dropout occurs before the clinical trial ends, the most recent data will be analyzed as if it were obtained at that point in time (Last Observation Carried Forward Analysis). The SG analysis will be conducted to assess safety. All statistical analyses will be performed with SPSS version 21.0; no interim analyses will be performed.

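### The full analysis set drops randomised patients with no scan on treatment and lets eligibility violators be excluded, so unscanned early failures leave the primary DCR denominator

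*Protocol article*

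**What the plan says.** All references are to the protocol article.

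- **Entry to the full analysis set (FAS), section 2.10.1:** "The FAS group will include participants who received the clinical trial medication, followed by one or more measurements of the primary outcome".
- **Further removals, same section:** "Participants in FAS group who violate major inclusion, exclusion criteria or have never taken drug for clinical trial can be excluded".
- **Role of the set, section 2.11:** "The main analysis will be the FAS group analysis for the validity evaluation". The per-protocol (PP) analysis is run beside it, and the PP set is a subset of the FAS. The safety group contains everyone who took HAD-B1 or placebo at least once, but it is used for safety only.
- **Missing data, section 2.11:** "For the FAS group, if a defect value happens at any point or a dropout occurs before the clinical trial ends", the most recent value is used in its place (last observation carried forward, LOCF).
- **Primary outcome, section 2.6:** DCR, "which will be assessed from the date of randomization to 12 weeks, as determined by chest X-ray, CT or MRI according to the RECIST criteria". The earliest post-baseline time given for any outcome is in the next paragraph, where the secondary outcomes, including CR, PR and SD, are compared "after 6 weeks and 12 weeks compared to baseline".
- **Expected losses:** section 2.5 foresees that "the trial may be terminated before the end of 12 weeks due to the development of unacceptable toxicities or withdrawal" of the participant. Section 2.9 plans for 30% dropout in each group.

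**The concern.** A full analysis set should stay as close as possible to the groups as randomised. Here a patient enters the main analysis only by staying on study long enough to be imaged. Those who do not get that far are likely to include the worst outcomes: early death, clinical deterioration, and stopping for toxicity. They are not scored as failures. They leave both numerator and denominator, and the DCR rises.

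If the arms lose patients before imaging at the same rate, every arm's DCR is too high. If the rates differ, the arm that loses more looks better. That is awkward in a trial meant to choose between two doses, where tolerability may itself differ by dose.

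The eligibility clause adds a different problem. Removal from the main set is optional, and nothing in the clause prevents the decision from being made when the patient's outcome is already known.

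**Working it through.** **1. Can an unscanned patient get back in?** Take a patient who is randomised and dosed, and who stops before any post-baseline imaging.

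- FAS (2.10.1): not a member, because there is no later measurement of the primary outcome.
- LOCF (2.11): applies only to FAS members, and this patient has no post-baseline value to carry.
- PP (2.10.1): not a member, because PP is a subset of the FAS.
- Safety group: a member, but it carries no efficacy analysis.

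No stated efficacy analysis includes this patient. A patient whose progression is seen on a scan does stay in and counts as a failure. The problem is confined to patients with no scan at all.

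**2. The plan's own figure.** Section 2.9 states that "the total number of participants required for each group was calculated as 15, for a total of 45". Inflating for dropout: 15/(1 − 0.30) = 21.43, rounded up to 22 per group, and 3 × 22 = 66. This reproduces. Total dropout is 0.30 × 22 = 6.6, so about 7 per arm is the upper limit on losses before the first scan. The article does not say how many of these precede a scan.

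**3. Effect on a single arm.** Let *p* be the DCR among scanned patients and *m* the share with no scan. The FAS reports *p*. With unscanned patients counted as not controlled, the DCR over all randomised is *p*(1 − *m*). The overstatement is therefore *p* × *m*. Both inputs are assumptions, so a range is shown:

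| Share with no scan (*m*) | Overstatement for *p* = 0.80 to 0.95 |
|---|---|
| 5% | 4.0 to 4.8 points |
| 10% | 8.0 to 9.5 points |
| 15% | 12.0 to 14.2 points |
| 30% (all dropout before a scan, upper bound) | 24.0 to 28.5 points |

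In patients: if half of the 30% dropout comes before the first scan (assumed), 0.15 × 22 = 3.3, or about 3 patients. With 15 controlled, the FAS gives 15/(22 − 3) = 15/19 = 78.9%, against 15/22 = 68.2% over all randomised, a gap of 10.8 points.

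**4. Effect on the comparison.** Equal loss in both arms with equal DCR creates no difference between them; unequal loss does. In each case below the two arms are identical over all randomised patients, and every unscanned patient is taken to be a failure.

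| Assumed case | All randomised, both arms | FAS, arm with more unscanned | FAS, other arm | Chi-squared p (uncorrected) |
|---|---|---|---|---|
| 14 controlled; 5 vs 1 unscanned | 14/22 = 63.6% | 14/17 = 82.4% | 14/21 = 66.7% | about 0.27 |
| 16 controlled; 5 vs 1 unscanned | 16/22 = 72.7% | 16/17 = 94.1% | 16/21 = 76.2% | 0.13 |
| 16 controlled; 6 vs 0 unscanned (extreme) | 16/22 = 72.7% | 16/16 = 100% | 16/22 = 72.7% | 0.023 (Fisher 0.030) |

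The first row gives 82.4 − 66.7 = 15.7 points of difference produced by exclusion alone.

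**5. The eligibility clause.** It lets FAS members be removed for major violations and, redundantly, for never having taken study drug, which the entry rule already requires. Violators are not early failures as such, so this clause does not feed the figures above. Its weakness is that removal is optional and sits in the main set.

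**The case against.** The strongest reply has five parts.

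- **The numbers are assumed.** The article gives total dropout only, not dropout before a scan, and nothing in it supports a 5 versus 1 imbalance. This stands: the figures show what the rule can do, not what it will do. At 5 versus 1 neither example is significant; only the extreme case is.
- **The direction of any bias is unknown.** All arms take the same afatinib, and the Discussion (section 3) hypothesises that HAD-B1 reduces its toxicity. If so, more control patients would go unscanned and the rule would work against HAD-B1. This also stands, but bias in an unknown direction is no more acceptable when choosing a dose.
- **Blinding limits the eligibility exclusions.** Section 2.8 keeps the codes sealed until the end of the trial, so exclusions made during it are blind to arm. That is fair. Sealed codes do not hide the patient's outcome, however, and the clause still puts a discretionary exclusion in the main set.
- **Scoring unscanned patients as failures is a convention.** It treats withdrawal of consent like progression. That is true, and other handling is possible in sensitivity analyses. It does not justify leaving these patients out of every efficacy analysis.
- **The trial is exploratory, and the timing of the first scan is inferred.** The 6-week time is attached to secondary outcomes. An exploratory aim lowers the stakes, but section 2.13 formally tests DCR across the three groups and for each dose against placebo. The core point does not depend on week 6: whenever the first scan falls, patients lost before it are removed.

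A fuller analysis plan would not answer the point, because the article itself states the set's definition rather than leaving it open.

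**Conclusion.** The concern holds. As written, the main efficacy set excludes dosed patients who have no post-baseline tumour assessment, and no other efficacy analysis restores them. DCR is overstated by the scanned-patient DCR multiplied by the unscanned share: about 4 to 14 points for 5% to 15% unscanned, and up to 28.5 points if all planned dropout came before a scan. This assumes a DCR of 0.80 to 0.95 in scanned patients and counts unscanned patients as not controlled. Bias between arms arises when unscanned rates differ; its size and direction cannot be worked out from the article. An imbalance of 5 versus 1 can produce a difference of about 16 points between arms with identical results. The optional removal of eligibility violators is a separate, smaller defect in the same definition.

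**What to change.** In section 2.10.1:

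1. Define the main set as all randomised participants, analysed in their assigned arm. Leaving out only those who never took blinded study drug is acceptable.
2. State that a participant with no post-baseline scan counts as not disease-controlled. This must accompany the first change. Otherwise the LOCF rule could be read as carrying baseline forward, and no change from baseline might be scored as stable disease and so as control.
3. Delete the optional eligibility exclusion from the FAS. Apply it to the PP set only, with membership decided before unblinding.

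The cost is wording: 22 per arm and 66 in total are unchanged, and no new data are needed. Reported DCRs will be lower by the amounts shown above, which may be more than slight if early loss is common. Reporting the number unscanned in each arm, with reasons, would let readers judge the effect. The change should be made before unblinding, because it will not be credible afterwards.

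### The per-protocol set requires completion of the 12-week trial and has no rule keeping participants who leave early through progression or death, so it partly selects on the primary outcome

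*Protocol article*

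**What the plan says.** Section 2.10.1 defines two efficacy sets.

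- FAS: "The FAS group will include participants who received the clinical trial medication, followed by one or more measurements of the primary outcome".
- PP: those in the FAS "who successfully completed this clinical trial according to the trial plan". A separate sentence adds adherence exclusions: "Participants in PP group who violate test plan or take forbidden drug or do not obey a schedule can be excluded".

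Section 2.11 gives the sets their roles. On the FAS: "The main analysis will be the FAS group analysis for the validity evaluation". After a missing value or a dropout in the FAS, "the most recent data will be analyzed as if it were obtained at that point in time (Last Observation Carried Forward Analysis". On the PP set: "The PP group analysis will be carried out separately to evaluate whether or not any differences from the FAS analysis results exist".

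Section 2.6 sets the primary outcome, DCR, "which will be assessed from the date of randomization to 12 weeks, as determined by chest X-ray, CT or MRI according to the RECIST criteria". Section 2.13 names its components as complete response, partial response and stable disease, so progression is failure. Section 2.6 also places the secondary comparisons, including response and progression-free survival (PFS), at weeks 6 and 12. Section 2.5 gives 12 weeks of treatment and names unacceptable toxicity and participant withdrawal as reasons for an earlier end. It does not mention progression.

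**The concern.** Completion is required in addition to adherence, because the adherence exclusions stand in their own sentence. Completion is settled after randomization, over the same 12 weeks in which the primary outcome is determined. A participant may follow the plan fully, progress at the week-6 assessment and then leave. That participant is an observed failure of the primary endpoint and has broken no rule, yet is not a completer. A participant who dies after the week-6 assessment cannot complete on any reading. Nothing in the article keeps either of them in the PP set.

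The PP analysis has one job, which is to show whether the result changes from the FAS. If the PP set has lost failures, a difference from the FAS may reflect that loss instead of adherence, and agreement is not clearly reassuring. If early leaving differs between arms, the PP comparison between arms can also be distorted in either direction.

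**Working it through.** The article gives no PP figure to reproduce. Its only related figure is the group size in section 2.9: 15/(1 − 0.30) = 21.43, rounded up to 22, and 3 × 22 = 66. This reproduces.

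**Step 1: one participant under both sets.** Take a participant with progression at week 6 who then leaves, and assume that the week-6 assessment counts as a measurement of the primary outcome.

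- FAS: included, with progression carried forward to week 12, so a DCR failure.
- PP: not a completer, so absent.

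A participant who dies before week 12 is also absent from PP. If progression was documented first, the FAS counts a failure. If not, carry-forward would use the last assessment, and the article does not say how the death is counted.

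**Step 2: general formula.** Let p be the true week-12 DCR and q the share of DCR failures who leave before week 12 and so drop out of PP. Neither is given in the article. Then

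PP DCR = p / [p + (1 − p)(1 − q)].

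With assumed true DCRs of 70% and 90% and the same q in both arms:

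| q | PP DCR, p = 70% | PP DCR, p = 90% | Difference (points) |
|---|---|---|---|
| 0 | 70.0% | 90.0% | 20.0 |
| 0.25 | 75.7% | 92.3% | 16.6 |
| 0.5 | 82.4% | 94.7% | 12.4 |
| 0.75 | 90.3% | 97.3% | 7.0 |
| 1 | 100% | 100% | 0 |

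With unequal q and no true effect (p = 80% in both arms, q = 0.25 and 0.75):

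- 0.80/(0.80 + 0.20 × 0.75) = 84.2%
- 0.80/(0.80 + 0.20 × 0.25) = 94.1%

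That is a false difference of 9.9 points.

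**Step 3: a size tied to the article's own median.** The Discussion gives a median PFS of 9–12 months under EGFR inhibitors. Assume exponential PFS, assessments at weeks 6 and 12, and that every week-6 progressor leaves. Six weeks is 1.38 months and twelve weeks is 2.76 months.

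- True week-12 DCR, exp(−ln 2 × 2.76/m): 0.809 for m = 9 and 0.853 for m = 12.
- PP DCR, exp(−ln 2 × 1.38/m), i.e. no progression by week 12 given none at week 6: 0.899 and 0.923.
- Failures in total: 1 − 0.809 = 19.1% and 1 − 0.853 = 14.7%.
- Failures removed at week 6: 1 − 0.899 = 10.1% and 1 − 0.923 = 7.7%, about half of the total.

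With a further assumed hazard ratio of 0.5, the true difference is 0.091 (m = 9) or 0.071 (m = 12). The PP difference is 0.049 or 0.038. The loss is 4.2 or 3.3 points.

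**Step 4: in participants.** Removing 7.7–10.1% of an arm is 1.7–2.2 of 22, or 1.2–1.5 of 15. One participant is 1/22 = 4.5 points or 1/15 = 6.7 points.

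**The case against.** The strongest objection is that early departure after progression is assumed. Section 2.5 lists toxicity and withdrawal as reasons for an early end, not progression. If all progressors stay to week 12, q = 0 and progression causes no distortion. Early deaths should also be few, since section 2.3 requires a life expectancy above six months. This stands: it makes the size unknown. It does not supply a rule that keeps early failures in PP, and a progressor may leave by withdrawing.

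The effect is also small in participants: one or two per arm in step 3, with the between-arm shrinkage below one participant's worth. That stands too, and it limits the weight of the point.

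A full protocol or statistical analysis plan, not shown here, may treat early progressors in more detail. But the article states a completion rule, and that rule is what needs changing.

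Two further complaints are not supported. Leaving out participants who stop for toxicity is a conventional feature of a PP set. When the exclusion list is fixed relative to unblinding is a detail that an article may leave to the analysis plan.

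**Conclusion.** The point holds as a defect in a secondary analysis. The PP set partly selects on the primary outcome, PP DCR is biased upward to the extent that failures leave early, and the FAS–PP comparison cannot be reliably interpreted. The distortion ranges from none, if no progressor leaves, to a PP DCR of about 90–92% against 81–85%, if all week-6 progressors leave. The upper figure rests on exponential PFS, the 9–12 month median, a week-6 assessment and departure at progression. The article states only the median and the timing of the secondary comparisons.

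A reader might infer more, in three ways that the article does not support.

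- PP DCR would be 100% in every arm. This needs successful completion to mean treatment success. The natural meaning is completing the trial as planned, so progression first seen at week 12 stays in PP as a failure.
- The PP analysis is useless as a check. PP also excludes for plan violation, forbidden drugs and schedule, so a difference from the FAS would mix adherence with lost failures. It is informative when few progressors leave.
- The main result is compromised. The FAS is the main analysis and the PP definition does not touch it, nor does it affect the sample size.

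This is a cheap improvement.

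**What to change.** In section 2.10.1, and in the analysis plan, replace the completion requirement. Define PP by adherence and absence of major protocol deviations up to week 12, documented progression or death, whichever comes first. State that participants who stop because of progression or death remain in the PP set and count as DCR failures. Deaths without documented progression should be counted the same way in both sets, so that the FAS and PP results differ only through membership.

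The cost is a sentence or two of text. The PP DCR will be somewhat less favourable. The sample size and the choice of main analysis set do not change.

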### Principles of interpretation of results

2.11

The main analysis will be the FAS group analysis for the validity evaluation. The PP group analysis will be carried out separately to evaluate whether or not any differences from the FAS analysis results exist. For the FAS group, if a defect value happens at any point or a dropout occurs before the clinical trial ends, the most recent data will be analyzed as if it were obtained at that point in time (Last Observation Carried Forward Analysis). The SG analysis will be conducted to assess safety. All statistical analyses will be performed with SPSS version 21.0; no interim analyses will be performed.

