### Analysis of first outcome variables

2.13

Descriptive statistics (number in each group, average, standard deviation, minimum value and maximum value) will be used for each variable affecting the DCR (CR, PR, and SD), and the results for the two test groups and the control at the last visit versus the results at baseline will be presented. The statistical significance of any difference found between test groups and the placebo group will be analyzed using chi squared test. If any difference among three groups (2 test groups and 1 placebo group) is found, Bonferroni or Duncan method will be used. Chi squared test between placebo group and treatment group 1, placebo group and treatment group 2 will be additionally conducted.

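### Last observation carried forward in the main analysis counts a participant who leaves after a non-progressed scan as controlled at week 12, so the primary DCR can be overstated but never understated

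*Protocol article*

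**What the plan says.** All references are to the protocol article.

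- **2.11, Principles of interpretation of results:** "The main analysis will be the FAS group analysis for the validity evaluation". Within that set, for a missing value or a dropout before the end of the trial, "the most recent data will be analyzed as if it were obtained at that point in time". The method is named as last observation carried forward (LOCF). No endpoint is exempted. The per-protocol (PP) analysis is the only other efficacy analysis.
- **2.6, Outcome measures:** the primary DCR is compared "after 12 weeks compared to baseline, which will be assessed from the date of randomization to 12 weeks". The secondary outcomes, which include CR, PR and SD, are compared "after 6 weeks and 12 weeks compared to baseline".
- **2.13, Analysis of first outcome variables:** CR, PR and SD make up disease control, and results "at the last visit versus the results at baseline will be presented".
- **2.10.1, Analysis group:** entry to the FAS needs trial medication followed by at least one measurement of the primary outcome. The PP set is limited to those who completed according to plan.
- **2.9, Sample size calculation:** "When a dropout rate of 30% was used for each group", 15 per group became 22.
- **2.5, Interventions:** "the trial may be terminated before the end of 12 weeks due to the development of unacceptable toxicities" or because the participant withdraws.

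**The concern.** Taken together, these sections mean that a participant with stable disease at an interim scan, who then stops for toxicity, withdraws or dies without another scan, enters the primary analysis as controlled at week 12. The favourable status is assumed where it was not observed.

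The error runs one way. Stable disease can become a partial response, but both count as control. Progression is the only change that matters, and a progressed patient does not return to control. Carrying a non-progressed scan forward is therefore either right or too favourable.

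Two things are at stake. The first is the level of DCR in each arm. The second is the comparison between arms in a trial meant to inform the dose. Toxicity is a named reason for stopping, and the Abstract and Discussion hypothesise that HAD-B1 reduces afatinib toxicity, so dropout may well differ by arm. The PP analysis does not test the rule, because it leaves out the participants whose values were filled in.

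**Working it through.** **The plan's own figure.** 15 / (1 − 0.3) = 21.43, rounded up to 22 per group; 3 × 22 = 66. This agrees with section 2.9. The planned loss is 22 − 15 = 7 per group.

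**Inputs.**
- Planned dropout: 30% in each group (2.9).
- Median PFS on EGFR-TKIs: 9 to 12 months (Discussion), or 39 to 52 weeks.
- Assumption: progression-free status follows an exponential curve with that median.
- Assumption: the scan carried forward is at week 6. This is inferred from the 6- and 12-week comparisons in 2.6, because the schedule table is not shown.

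**Formula.** Overstatement of an arm's DCR = f × p6 × q, where
- f is the share of the FAS that leaves after the week-6 scan;
- p6 is the probability of being progression-free at week 6;
- q is the probability that a dropout controlled at week 6 has progressed by week 12.

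With p(t) = exp(−t × ln 2 / median):
- Median 9 months: p6 = 0.899, p12 = 0.808, q = 1 − 0.808/0.899 = 0.101.
- Median 12 months: p6 = 0.923, p12 = 0.852, q = 0.077.

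**Overstatement if all 30% leave after the week-6 scan (f = 0.30).**

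| Dropouts after week 6 | Median 9 months | Median 12 months |
|---|---|---|
| Progress like others | 0.30 × 0.899 × 0.101 = 2.7 points | 0.30 × 0.923 × 0.077 = 2.1 points |
| Three times the hazard | 7.4 points | 5.9 points |
| All have progressed (q = 1) | 27.0 points | 27.7 points |

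**If only half of the dropouts have a week-6 scan.** The others leave the FAS under 2.10.1, so f = 0.15/0.85 = 0.176. The overstatement is then 1.6, 4.3 and 15.9 points at 9 months, and 1.3, 3.5 and 16.3 points at 12 months, for the same three cases.

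**Between arms.** With 30% dropout in both arms and equal progression, the net bias is 0. With an assumed 40% against 20% and equal progression, the higher-dropout arm gains 1.8, 4.9 or 18.0 points at 9 months, and 1.4, 3.9 or 18.5 points at 12 months.

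The direction depends on dropout times progression among dropouts. With p6 = 0.9, dropout of 35% with q = 0.05 gives 0.35 × 0.9 × 0.05 = 1.6 points. Dropout of 30% with q = 0.10 gives 0.30 × 0.9 × 0.10 = 2.7 points. Here the arm with more dropout gains less.

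**Effect of counting dropouts as not controlled.** With all 30% leaving after week 6, DCR is (1 − f) × p12 + f × p6 under LOCF and (1 − f) × p12 under the alternative:
- 9 months: 83.5% falls to 56.6%.
- 12 months: 87.3% falls to 59.7%.

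This rule has its own error. Take 40% against 20% dropout, a median of 9 months, no true difference, and dropouts who progress like others. It shows (0.60 − 0.80) × 0.808 = −16.2 points, where LOCF shows +1.8.

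**The rule can decide the ranking.** As an assumed example, take 22 per arm, with 9 against 4 dropouts, all SD at week 6, and 10 of 13 against 14 of 18 completers controlled. LOCF gives 19/22 = 86% against 18/22 = 82%. Counting dropouts as not controlled gives 10/22 = 45% against 14/22 = 64%.

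**The case against.** The strongest reply is that the likely bias is modest. On the article's own median PFS, only about 8% to 10% of those controlled at week 6 progress by week 12, so ordinary dropout costs 2 to 3 points. Dropouts whose last scan shows progression are correctly carried forward as failures, and those with no post-baseline scan are not carried forward at all. The trial is labelled exploratory. All of this stands, and it limits the size.

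The endpoint wording also leaves room for doubt. The phrase about assessment from randomization to 12 weeks could mean response at any time in the period, and then a week-6 SD would count even without LOCF. The references in 2.6 to the state after 12 weeks, and in 2.13 to the last visit, favour the week-12 reading.

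Three stronger readings are tempting, and the document does not support them.

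- **A bias of about 30 points.** With 12 of 15 completers controlled and 7 dropouts, one can set (12 + 7)/22 = 86% beside 12/22 = 55%. That is the gap between two extreme imputations. It is a bias only if every dropout had a controlled scan and then progressed.
- **The rule favours the arm with more dropout.** The plan assumes 30% in each group, which by itself gives no net bias if progression is equal. The direction is conditional, as shown in the working.
- **Dropouts are treated as progression-free to week 12 in PFS and TTP.** The rule's wording is unrestricted, but nothing says that event times are filled in this way or that censoring is excluded. Censoring rules may stand in a document that is not shown.

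**Conclusion.** The point holds in a bounded form. Section 2.11 fixes LOCF for the main analysis and does not exempt the primary endpoint, so this is a stated choice and not a detail left open. It can only equal or overstate week-12 DCR.

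If all planned dropout follows a week-6 scan, the overstatement is about 2 to 3 points when dropouts progress like others, about 6 to 7 points at three times the hazard, and at most about 27 to 28 points. It is smaller if some dropouts have no post-baseline scan. These sizes rest on the exponential curve, the quoted median PFS, the inferred week-6 scan and the week-12 reading of the endpoint.

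Bias between arms is plausible, because toxicity can end treatment and the trial expects HAD-B1 to change toxicity. The document does not establish that it will occur or which arm would gain. The planned PP comparison would not reveal it.

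**What to change.** - In 2.11 and 2.13, replace LOCF for the primary DCR: an FAS participant without a week-12 assessment showing CR, PR or SD counts as not controlled.
- State that this is a conservative convention which can itself mislead when dropout differs by arm.
- Report the last-scan (LOCF) result, and results over a range of assumptions about progression among dropouts, as sensitivity analyses.
- Add one sentence saying that LOCF does not apply to PFS or TTP.

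The cost is wording and a few extra tables; no new data are needed. The drawback is that DCR will look less favourable in every arm: on the assumptions above, 57% to 60% instead of 84% to 87% if all planned dropout follows the week-6 scan.
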